**Sustained Attention**

To verify the attentional component, we will perform a sustained attention response task. The test will always be at the same time to avoid influences from the circadian rhythm (RICCIO et al., 2002; VALDEZ et al., 2005). This test basically consists of the participant's use of the dominant hand to press the space bar on the keyboard in front of them when any digit, except the digit 3, appears on the computer screen. Thus, the participant must inhibit his response during the appearance of the digit 3 (ROBERTSON et al., 1997). The number of correct answers and response time will be measured in the two session that will be performed before and after the intervention. The e-prime software will be used for the programming and application of the test.

**Questionnaires**

The questionnaires described below will be applied before, during and after the interventions.

**Multidimensional Assessment of Interoceptive Awareness - MAIA**

Questionnaire designed to measure the ability to identify emotions and interoceptive bodily sensations (MEHLING, 2012). Items fall into some domains that refer to the following factors:

1) Awareness of bodily sensations.

2) Emotional reaction and attentional response to bodily sensations.

3) Emotion regulation capacity.

4) Consciousness of Mind-Body Integration.

5) Confidence in bodily sensations.

The instrument contains 32 items and has an internal consistency of 0.82. We will work on validating this questionnaire for the Brazilian population and using the version translated into Portuguese (MAIA-VB2).

Mindful Attention Awareness Scale (MAAS)

Scale that assesses the level of Mindfulness, consisting of 15 items, on a six-point Likert scale ranging from (1) almost always to (6) almost never. The scale is one-dimensional, so all items measure Mindfulness. We will use the Brazilian version of the questionnaire (ATANES et al., 2012) and we will work on validating this version.

**FFMQ- Five Facets of Mindfulness Questionnaire - (FFMQ)**

This scale assesses the level of Mindfulness and is composed of 39 items on a five-point Likert scale ranging from (1) never or rarely true to (5) almost always or always true. On this scale, the concept of Mindfulness is divided into five components, they are:

(1) Observing, which includes noticing or being aware of internal and external experiences, such as sensations, cognitions, emotions, sights, sounds and smells.

(2) Describe, which refers to characterizing internal experiences through words.

(3) Acting with awareness, which refers to being aware of the activities of the moment and can be contrasted with mechanical behavior while attention is focused on something else, known as autopilot.

(4) Non-judgment of internal experience, which refers to not taking an evaluation and judgmental stance in relation to thoughts and feelings.

(5) Non-reactivity to internal experience, which refers to the tendency to allow thoughts and feelings to come and go without being affected or taken over by them (BAER et al., 2006). We will use the Brazilian version of the questionnaire (BARROS et al., 2014).

**State Mindfulness Scale - (SMS)**

This scale aims to assess levels of mindfulness related to the state of consciousness (TANAY; BERNSTEIN, 2013). It was developed based on previous mindfulness trait scales and seeks to complement the mindfulness assessment at the time of its application. It is a scale that contains 21 items where the individual will have to answer the questions with a graduation from “nothing” to enough”. We will work on validating this scale for the Brazilian population.

**Perceived Stress Scale**

The Perceived Stress Scale - PSS (COHEN, 1983) is one of the most cited instruments in the literature for stress estimation. PSS assesses stress under three aspects: presence of specific agents that cause stress, physical and psychological symptoms of stress and general perception of stress, regardless of its causative agent (for example, in item 3: "In the past month, how often have you did you feel nervous or stressed?”). According to the authors, other instruments available in the literature intend to estimate the specific impact of some stressful factors, which limits their results as stress-related events can vary between individuals. In this study, we will use the short version of this scale translated and validated for the Brazilian population (DIAS et al., 2015)

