**2. Objectives**

General:

• Assess the impact of a brief training on the stress response, interoception and well-being on healthy individuals.

Specific:

• Verify the relationship between mindfulness trait and hypothalamic-pituitary-adrenal axis reactivity.

• Analyze the neuroendocrine response to a stress event after a brief mindfulness-based intervention.

• Assess the impact of mindfulness practice (3 days) on the attention system, autonomic nervous system, and interoceptive ability.

• Check the influence of the practice on self-report measures of stress, anxiety, and affect

• Assess participants' electroencephalographic activity before and after the proposed intervention, during a sustained attention test, an interoception test, and during the stress test.

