**Training**

Based on previous studies, a brief intervention will be performed for 3 days for 30 minutes a day, involving practices contained in the mindfulness program for stress reduction. The exercise used in the study will be a practice of attention focused on the sensations of breathing that will be recorded by a qualified professional. The participant will come to the laboratory during the morning for 3 consecutive days and must stay in a room dedicated to practices throughout the procedure. The control group will spend the same time in a room designated for the study and will be subjected to a task of coloring figures during the same time as the experimental group. The study steps are specified in the diagram below:

Figure 1: Timeline of assessments throughout the study of groups 1 and 2. EEG: Electroencephalography.

In a schematic way, the evaluation with the EEG will be carried out as follows:

Figure 2: Schematic showing the activities to be performed during data acquisition using electroencephalography (EEG).

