**Dosage of salivary cortisol**

Salivary cortisol dosages will be performed from samples collected on day 3 of the protocol. They will be made using commercial dosage kits from the company DRG Instruments GmbH (Germany).

The basic principle used by the kit is the competition ELISA, in which a microplate is sensitized with monoclonal antibodies (IgG) to cortisol. The reading of samples will be performed by spectrophotometry.

On day 1 of the protocol, the participant will answer the pre-intervention questionnaires and a blood sample will be collected for subsequent analysis of cortisol and BDNF.

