**Positive and Negative Affect Schedule - (PANAS)**

This questionnaire consists of a set of words that describe different feelings and emotions arranged in two mood scales with 10 items each (WATSON; CLARK; TELLEGEN, 1988). Each item is scored from 1 to 5 points (1 = "very slightly or not at all" to 5 = "extremely") to indicate the extent to which respondents felt feelings and emotions during the weeks prior to the interview. We will use the version validated in Portuguese by (GALINHA; PAIS-RIBEIRO, 2005).

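### PSS and PANAS, as described, look back over a month and over weeks, so repeating them around a 3-day intervention heavily dilutes the self-reported stress and affect comparisons

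*Protocol*

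**What the plan says.** One specific aim in section 2 (Objectives) is to "Check the influence of the practice on self-report measures of stress, anxiety, and affect". Under Training, "a brief intervention will be performed for 3 days for 30 minutes a day", and "The participant will come to the laboratory during the morning for 3 consecutive days". Under Questionnaires, one sentence governs every scale: "The questionnaires described below will be applied before, during and after the interventions". The section on salivary cortisol places the baseline: "On day 1 of the protocol, the participant will answer the pre-intervention questionnaires".

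Two of the scales that serve this aim are described with long recall periods. The PSS section gives an example item, "In the past month, how often have you did you feel nervous or stressed". The PANAS section says items are scored "to indicate the extent to which respondents felt feelings and emotions during the weeks prior to the interview", without saying how many weeks. Nothing in the text shortens either period for the repeated administrations. The last dated assessment in the text is the saliva sampling on day 3, and no later follow-up is described.

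**The concern.** A repeated self-report scale can register an intervention only to the extent that its recall period covers time after the intervention began. Here the period is a month or some weeks and the intervention takes three days. The later rating therefore asks mainly about days before the first session, most of which the participant has already rated at baseline.

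At stake is the interpretation of two of the three constructs in the objective. If the arms do not differ on PSS or PANAS, the reader cannot tell whether the practice had no effect or the questions looked at the wrong days. This is settled when the form is filled in. No later analysis can recover a rating of the intervention days that was never asked for.

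**Working it through.** The protocol gives no figure for recall coverage, so there is none to reproduce. Its sample-size statement (f = 0.3, alpha 0.05, 80% power, correlation 0.6, at least 40 participants, 50 recruited) serves below only as a yardstick. The 40 can be neither confirmed nor refuted, because the number of measurements, the effect-size option and the loss rate are not given. The point does not rest on it.

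**Inputs**
- PSS window W: past month, taken as 30 days.
- PANAS window W: weeks, number not given; assumed two to four, so 14 to 28 days.
- Time since the first session at a day-3 assessment, d: 2 days elapsed, or 3 if both end days are counted.

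**Step 1. Share of the window after the first session, d/W**
- PSS: 2/30 = 6.7% to 3/30 = 10%.
- PANAS: 2/28 = 7.1% to 3/14 = 21.4%.

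**Step 2. Share before the first session, (W - d)/W.** This is also the overlap with the window rated on day 1.
- PSS: 27/30 = 90% to 28/30 = 93%.
- PANAS: 11/14 = 79% to 26/28 = 93%.

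Steps 1 and 2 are the finding. Step 3 only illustrates what they could mean for power.

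**Step 3. Illustration, assuming respondents weight all days in the window equally.** Then the diluted effect is 0.3 x d/W. For a group-by-time interaction with k = 2 groups and m = 2 measurements (assumed), the noncentral F has lambda = f² x N x m / (1 - rho), with 1 and N - 2 degrees of freedom. With rho = 0.6:

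| Scale and window | d | Diluted f | Power, N = 40 | Power, N = 50 |
|---|---|---|---|---|
| No dilution | - | 0.300 | 98.5% | 99.6% |
| PSS, 30 days | 2 | 0.020 | 5.9% | 6.1% |
| PSS, 30 days | 3 | 0.030 | 7.0% | 7.5% |
| PANAS, 28 days | 2 | 0.021 | 6.0% | 6.3% |
| PANAS, 28 days | 3 | 0.032 | 7.3% | 7.9% |
| PANAS, 14 days | 2 | 0.043 | 9.1% | 10.2% |
| PANAS, 14 days | 3 | 0.064 | 14.4% | 16.9% |

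For example, PSS with d = 3 and N = 40: lambda = 0.03² x 40 x 2 / 0.4 = 0.18.

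**Step 4. Sensitivity to the correlation.** Overlapping windows should push the pre-post correlation above 0.6. At an assumed rho of 0.9 and d = 3, power for PSS is 13.1% (N = 40) and 15.3% (N = 50). For PANAS with a 14-day window it is 42.6% and 51.3%.

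**The case against.** The strongest case on the other side has four parts.

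- **The design is randomised with a time-matched colouring task.** Re-test effects should be similar in both arms. A reader might infer that any change on these scales must be a re-test or demand artefact; the documents do not support that for the comparison between arms. A difference could be a real effect, or current mood colouring recall, which may itself follow from the intervention. This stands. Randomisation prevents bias, however, not dilution, and it does not protect the within-group tests that the Statistical analysis section also plans.
- **Equal weighting of days is a model.** Recent days may count for more. A reader might infer that the required sample rises 100- to 225-fold (1/0.10² to 1/(2/30)²). That needs both linear averaging and an unchanged correlation. At rho = 0.9 the same scaling is multiplied by 0.1/0.4, giving about 25 to 56. The multiplier should not be quoted as a property of this trial. The introduction also cites a study in which three days of practice improved perceived stress against a control group. It names no instrument or recall period, so it neither rescues nor refutes the PSS here, but it argues against calling a null result inevitable.
- **The schedule is incompletely visible.** The timeline figure is not shown. The sentence on questionnaire timing covers every scale, trait scales included, and does not tie each to a visit. The month window is seen in one example item, and the PANAS weeks are not counted. A post-intervention questionnaire given weeks later would weaken the point, though the text describes none.
- **Other measures exist.** The STAI has a state part, and salivary cortisol, heart rate variability and skin response address the stress response. This stands and limits the point to self-reported stress and affect.

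**Conclusion.** The point holds for the self-reported stress and affect parts of one specific objective. As the protocol reads, about 90-93% of the PSS window and about 79-93% of the PANAS window at a day-3 assessment lie before the first session. The comparisons are heavily diluted, and a null result on them would be uninformative.

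This rests on a month of 30 days, on PANAS weeks meaning two to four, and on a post-intervention questionnaire at or near day 3. The power figures rest further on equal weighting of days and two measurements. They are least secure for a short PANAS window with a high correlation.

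A reader might go further and conclude that the objective cannot be answered at all, or that a null result is built in. The documents do not support either. Anxiety keeps a state measure, the physiological outcomes are untouched, and a difference between arms on PSS or PANAS remains possible and would not automatically be spurious. The matter should be corrected, but it does not undermine the trial's other objectives.

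**What to change.** - **PANAS section:** specify a momentary instruction (how the participant feels right now) at each assessment.
- **Questionnaires and PSS sections:** keep the past-month PSS on day 1 as a baseline descriptor or covariate. For the repeated stress measure, use items re-anchored to the time since day 1, or a brief momentary stress rating. Restricting PSS to baseline without such a replacement would leave the stress part of the objective with no repeated self-report measure.
- **State Mindfulness Scale:** report it as a mindfulness measure, not as a stress or affect outcome.

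The cost is an instruction line on the forms, possibly one short added rating, and a few sentences in the protocol. The downside is that re-anchored or momentary scores are not directly comparable with scores obtained under the standard recall windows.

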**Positive and Negative Affect Schedule - (PANAS)**

This questionnaire consists of a set of words that describe different feelings and emotions arranged in two mood scales with 10 items each (WATSON; CLARK; TELLEGEN, 1988). Each item is scored from 1 to 5 points (1 = "very slightly or not at all" to 5 = "extremely") to indicate the extent to which respondents felt feelings and emotions during the weeks prior to the interview. We will use the version validated in Portuguese by (GALINHA; PAIS-RIBEIRO, 2005).

**Amsterdam Resting-state Questionnaire- ARSQ**

This instrument aims to assess the relationship with thoughts in a state of rest. Developed by Diaz et al., 2013 and improved in 2014 (ALEXANDER DIAZ et al., 2014; DIAZ et al., 2013), it seems to be of great value when applied to participants undergoing contemplative practices. Version 2.0 to be used in this study consists of 54 items that should be answered on a scale of 1-5 that varies from “completely disagree” to “completely agree”.

**State-Trait Anxiety Inventory - (STAI)**

This inventory seeks to assess through two parts, each containing 20 statements, anxiety state and trait. It was developed by Spilberg et al (1970) and translated and validated for the Brazilian population by Biaggio and Natalício (1979). The participant must respond on a scale of 1-4 and the total score for each scale ranges from 20 to 80, with higher values ​​being indicative of higher levels of anxiety.

**Statistical analysis**

Initially, Kolgomorov-Smirnov normality tests will be applied to determine if the data obey a normal distribution. Once this prerequisite is met, Student's t test (parametric variables) or Mann Whitney U test (non-parametric variables) will be applied to detect the occurrence of significant differences within group and ANOVA to evaluate between groups differences. Spearman's correlation test will also be applied to test the occurrence of correlations between variables (anxiety, affect, stress and mindfulness, trait and state).

An exploratory and confirmatory factor analysis will be performed to verify the domains and association between the factors existing in the questionnaires. The internal consistency of the factors will be verified using Crombach's Alpha and only saturation values ​​greater than 0.4 for the eigenvalues ​​will be computed for the item's participation in the investigated domain.

For the analysis of plasmatic and behavioral markers, correlation tests and multivariate analysis will be used.

For all tests, the significance level (p value) less than or equal to 0.05 will be considered.

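### The Mann-Whitney U test, which needs independent samples, is assigned to before/after comparisons within the same people, at a cost of up to about half the power

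*Protocol*

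**What the plan says.** The Statistical analysis section sets out three steps.

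- A gate: "Kolgomorov-Smirnov normality tests will be applied to determine if the data obey a normal distribution".
- A choice of test that follows from it: "Once this prerequisite is met, Student's t test (parametric variables) or Mann Whitney U test (non-parametric variables"), with the stated purpose of finding differences within group. The Mann-Whitney assignment reads in full: "Mann Whitney U test (non-parametric variables) will be applied to detect the occurrence of significant differences within group".
- The comparison of the arms: "ANOVA to evaluate between groups differences".

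The threshold for every test is "the significance level (p value) less than or equal to 0.05 will be considered".

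Other sections show what a within-group comparison is here. Under Sustained Attention, correct answers and response time are "measured in the two session that will be performed before and after the intervention". Under Questionnaires: "The questionnaires described below will be applied before, during and after the interventions". Under Blood collection, blood is drawn from each participant before and after the intervention. The sample-size paragraph under Participants assumes a repeated-measures ANOVA with a 60% correlation between measures.

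**The concern.** Mann-Whitney U compares two separate sets of people. The protocol applies it to two measurements on one set. A person's before and after values are positively correlated, so the change within a person varies much less than the difference between two unrelated people. A test that ignores the pairing judges the change against too large a standard error.

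The same holds for Student's t if it is run in its two-sample form, and the text does not say which form is meant. Because the protocol names a specific test and that test does not fit the data, this is not detail left open for a later analysis plan.

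At stake are the protocol's before/after aims (attention, self-report measures, EEG before and after the intervention) in a trial of 50 people, where wasted power is hard to recover. The gate sentence is a second fault: taken literally, it sends non-parametric variables to Mann-Whitney only after normality has been met.

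**Working it through.** **Inputs.** Correlation between repeated measures 0.6, minimum 40 participants and recruitment of 50, all from Participants. Threshold 0.05 from Statistical analysis. Assumptions: 1:1 allocation (so 20 to 25 per arm), two-sided tests, bivariate normal data with equal SDs before and after, and a true change of 0.6 SD.

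**The plan's own figure.** The protocol gives no size or power for the within-group tests, so there is nothing to reproduce for this point. The figure of 40 is for a repeated-measures ANOVA interaction and serves here only to set the number per arm. The usual default formula for that interaction (f = 0.3, correlation 0.6, two time points) gives 20 in total, not 40. The number of time points is not stated, and this is a separate matter that does not affect what follows.

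**Step 1: hand check with the t test.**
- True SD of a within-person change: √(2(1 − 0.6)) = √0.8 = 0.894 SD.
- SD assumed by an unpaired test: √2 = 1.414 SD.
- Ratio: 0.894 / 1.414 = √0.4 = 0.632. Under no change, the unpaired statistic therefore has SD 0.632 instead of 1.
- On the correct scale, the 1.96 cut-off becomes 1.96 / 0.632 = 3.10. The two-sided tail beyond 3.10 is 0.0019, so the large-sample type I error is about 0.2% instead of 5%.
- Signal for a 0.6 SD change: 0.6√n / 0.894 = 3.00 at n = 20 and 3.35 at n = 25.
- Unpaired power: P(Z > 3.10 − 3.00) = 46% and P(Z > 3.10 − 3.35) = 60%.
- Paired power: P(Z > 1.96 − 3.00) = 85% and P(Z > 1.96 − 3.35) = 92%.

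These normal approximations slightly overstate power and understate the type I error at such small n.

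**Step 2: simulation of the tests themselves (20,000 runs per setting, correlation 0.6).**

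| n per arm | True change | Mann-Whitney | Signed-rank | Unpaired t | Paired t |
|---|---|---|---|---|---|
| 20 | 0.6 SD | 41% | 79% | 44% | 81% |
| 25 | none | 0.4% | 5.0% | 0.4% | 5.3% |
| 25 | 0.5 SD | 34% | 75% | 37% | 77% |
| 25 | 0.6 SD | 53% | 88% | 57% | 89% |

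At n = 20 with no change, Mann-Whitney rejects 0.44% of the time. Separate simulation runs put its power for 0.6 SD at 42% (n = 20) and 54% (n = 25).

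**Step 3: sensitivity to the correlation (n = 25, change 0.5 SD).** Over correlations of 0.4 to 0.8, Mann-Whitney's type I error falls from 1.2% to 0.01% and its power from 37% to 31%. Signed-rank power rises from 57% to 96%. The stronger the pairing, the greater the loss.

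**Step 4: the normality gate.** The protocol does not say whether Kolmogorov-Smirnov (KS) uses critical values corrected for an estimated mean and SD (Lilliefors), nor whether it is run per arm, pooled or on differences. Rejection rates for assumed lognormal data, per arm:

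| n | Log-SD | KS, uncorrected | KS, Lilliefors | Shapiro-Wilk |
|---|---|---|---|---|
| 20 | 0.5 | 1.5% | 35% | 48% |
| 20 | 0.7 | 5.9% | 55% | 75% |
| 20 | 1.0 | 19% | 79% | 93% |
| 25 | 0.5 | 2.4% | 42% | 63% |
| 25 | 0.7 | 9.8% | 65% | 87% |
| 25 | 1.0 | 31% | 88% | 97% |

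Pooled over 50 people, uncorrected KS rejects 11%, 39% and 81% at log-SD 0.5, 0.7 and 1.0.

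**The case against.** **The gate limits the damage.** If KS rarely rejects, Mann-Whitney is rarely reached. This stands in part. With uncorrected KS, a paired t test for data that pass, correlation 0.6, a 0.6 SD change and n = 20, the whole procedure had 80% power against 79% for always using signed-rank on normal data. On lognormal data it had 73% against 76% (log-SD 0.5) and 68% against 76% (log-SD 0.7). With Lilliefors values it fell to 57% against 76% at log-SD 0.5. So the full loss in the working applies to a variable that is actually sent to Mann-Whitney, or to an unpaired t test. The protocol excludes neither.

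**A reader might infer that the gate almost never triggers.** The document does not support that as a flat statement. It holds only for uncorrected KS, run per arm, on mild to moderate skew, and the protocol specifies neither the version nor the data tested.

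**A reader might also infer that the gate costs power in the biomarker comparisons between arms, or that missing log transforms are an error.** Neither follows. Between-group comparisons go to ANOVA with no rank alternative, so the gate does not route them. Plasma and behavioural markers are given correlation and multivariate methods. Transforms are ordinarily left to an analysis plan.

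**The authors may have swapped within and between.** Possibly, but nothing in the text shows it, and the sentence would still need correction.

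**Conclusion.** The point holds for the test assignment. The protocol names an independent-samples rank test for repeated measures on the same people, names no paired rank test, and leaves the form of the t test open. For a variable analysed this way, at the protocol's own correlation and 20 to 25 per arm, the type I error is about 0.4% instead of 5%. Power for a 0.6 SD change is about 42% to 54% where 79% to 88% is available. These figures rest on 1:1 allocation, two-sided testing and bivariate normal data.

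A reader might take wrong p-values to mean inflated false positives or a compromised main comparison. Neither is so: the error runs towards missed effects, and the ANOVA between the randomised arms is unaffected.

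The gate needs rewording because its condition is illogical as written and its version is unspecified. Its weakness against skewed data is conditional on how it is run.

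**What to change.** In Statistical analysis, replace the sentence on within-group tests with wording to this effect:

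- Before/after comparisons within a group use the paired t test, or the Wilcoxon signed-rank test when the paired differences are clearly non-normal. Mann-Whitney U is not used within group.
- Outcomes with more than two time points (salivary cortisol at four times on day 3; questionnaires before, during and after) are analysed with the repeated-measures model already used for the sample size under Participants.

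Reword the gate so that the parametric test follows when normality is acceptable and the rank test when it is not. If a formal check is kept, apply it to paired differences or model residuals and use Shapiro-Wilk or Lilliefors-corrected KS. Uncorrected KS rejects lognormal data of log-SD 0.5 to 0.7 only about 1% to 10% of the time at 20 to 25 per arm.

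The cost is a few sentences, matched in the statistical analysis plan if there is one. No procedure, visit, sample or participant number changes.

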**Dosage of plasma cortisol**

Cortisol levels will be determined in duplicate by the immunoenzymatically method (ELISA). Coefficients of variation will be calculated and must be less than 20%. The basic principle used by the kit is the competition assay, in which a microplate is sensitized with monoclonal antibodies (IgG) to cortisol. Unknown samples (from participants) compete with cortisol linked to a peroxidase enzyme for the cited antibodies. After an incubation period, unbound components are washed away. A substrate (tetramethylbenzidine) is added, and it will oxidize the cortisol-bound enzyme producing a color change. With the addition of a stop solution, another color change occurs and then a spectrophotometric reading will be taken using a filter with an adequate wavelength. It is noteworthy that using this type of ELISA, the higher the optical density, the lower the amount of hormone present in the sample, the opposite being true.

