**Autonomic Nervous System Assessment**

The measurement of the modulation of the Autonomic Nervous System (ANS) on the heart will be performed using the Heart Rate Variability (HRV) technique that uses the RR intervals of the electrocardiogram (ECG) captured and recorded for one hour with the volunteers in awake with electrodes connected to BrainAmp ExG (Brain Products GmbH, Munich, Germany).

Time and frequency domain measurements (HF (High frequency), LF (Low frequency), VLF (Very low frequency) and Ratio (LF/HF) will be used to represent cardiac vagal activity.

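### The only stated between-group test is ANOVA, and the only rank test is tied to within-group differences, so skewed salivary cortisol and HRV outcomes have no stated suitable between-group analysis and may lose power

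*Protocol*

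**What the plan says.** The Statistical analysis section begins with a Kolmogorov-Smirnov check: "normality tests will be applied to determine if the data obey a normal distribution". It then names a parametric test and a rank test, to be chosen by distribution. The purpose of that pair, and the method for comparing the arms, are given as: "to detect the occurrence of significant differences within group and ANOVA to evaluate between groups differences". The choice by distribution thus belongs to the within-group comparison, and ANOVA is the only method named between groups. No analysis scale or transformation is mentioned. A separate sentence covers blood markers: "For the analysis of plasmatic and behavioral markers, correlation tests and multivariate analysis will be used". The significance rule is common to everything: "For all tests, the significance level (p value) less than or equal to 0.05 will be considered".

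The outcomes affected are salivary cortisol, sampled once before and three times after the stress test (Saliva), and the heart rate variability measures, listed as "Time and frequency domain measurements (HF (High frequency), LF (Low frequency), VLF (Very low frequency) and Ratio (LF/HF" in Autonomic Nervous System Assessment. Under Participants, the trial is sized on a repeated-measures ANOVA with a within-between interaction, using f = 0.3, α = 0.05, 80% power and a correlation of 0.6. At least 40 participants are needed and 50 are to be recruited.

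**The concern.** The between-group comparison is the one that randomisation supports, and it is the one with no stated provision for skew. Hormone concentrations, spectral power and a ratio of two powers are positive quantities that often have a long right tail. On the raw scale a few high values then dominate both the group mean and its standard error, so a proportional effect is harder to detect.

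The rank test does not fill the gap as written. Mann-Whitney U compares independent samples, so it does not fit the paired before-after comparison to which it is assigned. Moved to the between-group comparison, it would still use one value per person and would not replace the group-by-time interaction on which the trial is sized.

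LF/HF has a further problem. A raw-scale verdict on LF/HF need not match the raw-scale verdict on its reciprocal from the same recordings. On the log scale the two differ only in sign and give the same p-value.

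**Working it through.** **Inputs.** From Participants: f = 0.3, α = 0.05, power 80%, correlation ρ = 0.6, N = 40 required and 50 recruited, two groups. Assumed, because the protocol does not state them: equal allocation, two-sided tests, m = 2 repeated measures, log-normal outcomes, and a log-scale SD between 0.3 and 1.2. The protocol gives no SD or distribution for any of these outcomes.

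**The protocol's own figure.** For the within-between interaction, λ = f²·N·m/(1−ρ), with df1 = m−1 and df2 = (N−2)(m−1) for two groups. With m = 2, N = 20 gives λ = 0.09×20×2/0.4 = 9 and power 0.81. With N = 40, λ = 0.09×40×2/0.4 = 18 and power is 0.985. The stated minimum of 40 is therefore not reproduced from these inputs (16 at m = 3 and 14 at m = 4, before loss). That is a separate matter and does not bear on this point. Here N = 40 is taken as given.

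**Check 1: one time point.** The group shift was set so that the log-scale t-test has 80% power (0.91 log-SD at 20 per arm, 0.81 at 25). The same simulated trials, at least 20,000 per cell, were then tested on the raw scale. With two groups, one-way ANOVA is the t-test.

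| Assumed log-SD | Log-scale power | Raw-scale power, 20 to 25 per arm |
|---|---|---|
| 0.4 | 80% | about 77% |
| 0.6 | 80% | about 73% |
| 0.8 | 80% | about 68% |
| 1.0 | 80% | about 61% |

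With no true effect, the raw test rejected in 3.6% to 5.1% of trials over log-SD 0.3 to 1.2, so there is no inflation. Mann-Whitney kept about 77% to 79% power throughout.

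**Check 2: the protocol's interaction scenario, N = 40, m = 2.** The interaction is a t-test on change scores with standardised difference √(4λ/N) = √(72/40) = 1.34. The SD of change is log-SD×√(2(1−0.6)) = 0.894 log-SD, so the shift is 1.34×0.894 = 1.2 log-SD.

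| Assumed log-SD | Log scale | Raw, effect raises outcome | Raw, effect lowers outcome |
|---|---|---|---|
| 0.5 | about 0.98 | 0.98 | about 0.86 |
| 0.7 | about 0.98 | 0.97 | 0.74 |
| 1.0 | about 0.98 | 0.90 | 0.54 |

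The asymmetry comes from the raw scale. At log-SD 0.5 the shift is 0.6 log units: upward this multiplies the outcome by e^0.6 = 1.82 (+82%), downward by e^−0.6 = 0.55 (−45%). The direction is not settled in advance: the Introduction cites a 3-day training study in which the mindfulness group had higher salivary cortisol than control.

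**Check 3: orientation of the ratio.** In the single-time-point trials at 20 per arm, raw LF/HF and raw HF/LF gave different significance verdicts in about 9%, 15%, 22% and 33% of trials at log-SD 0.3, 0.5, 0.7 and 1.0. In the interaction scenario the figures are about 13%, 26% and 45% at 0.5, 0.7 and 1.0. On the log scale disagreement is zero by construction.

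**Check 4: would the normality test catch the skew?** A Kolmogorov-Smirnov test with estimated mean and SD and no correction, applied to 40 log-normal values, rejects normality in about 6%, 27% and 64% of samples at log-SD 0.5, 0.7 and 1.0. At log-SD 0.5 and 0.7, most skewed samples would pass.

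**The case against.** The strongest reply is that the section does not commit the trial to raw values. It is silent on scale, and transformation is a detail that a separate analysis plan, not shown here, may supply. That stands: a reader might infer that untransformed analysis is planned, but the text does not say so. What the protocol does state is the assignment of tests, and that assignment is faulty as written.

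A reader might also infer that skewed data have no route at all, or that ANOVA applies whatever the distribution. The text does not support this either. ANOVA appears in a sentence conditioned on the normality check, and because Mann-Whitney U is an independent-samples test, the within and between labels may simply be swapped. If so, a rank route between groups exists, and at a single time point it recovers nearly all the lost power. It would still not test the interaction, and the normality check that selects it is weak at these sample sizes.

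Other stronger readings also fail:

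- Not every hormone outcome falls under the ANOVA rule. Plasma markers have their own sentence, although it names no between-group test and gives no route for skew.
- The numerator of the ratio is not an open choice: the protocol fixes LF/HF. The disagreement rates show that a raw verdict depends on that orientation, not that anyone plans to run both versions.
- The limit in Dosage of plasma cortisol, "Coefficients of variation will be calculated and must be less than 20" percent, is an assay quality limit on duplicates. It says nothing about the spread between participants.

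Finally, logging changes the target from a difference in means to a ratio of geometric means, and rank methods are an accepted alternative. That is a fair preference for a single time point, less so for the interaction.

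**Conclusion.** The point holds in limited form. As written, the between-group rule names only ANOVA, and the rank test is attached to a comparison it does not fit. Salivary cortisol, HF, LF, VLF and LF/HF are left without a stated between-group analysis suited to skewed positive data.

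The consequence is possible loss of power, not false positives. Under log-normality, the single-time-point loss runs from about 3 percentage points at log-SD 0.4 to about 19 at 1.0. In the interaction scenario it runs from negligible to about 44 points (0.98 to 0.54), depending on skew and on the direction of the effect. These sizes rest on an assumed log-SD, equal allocation and, for the interaction, two measures. If the real skew is slight, the loss is small. The change is worth making because it costs almost nothing and removes a dependence on scale and direction that serves no purpose.

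**What to change.** In the Statistical analysis section:

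1. State that salivary cortisol, HF, LF, VLF and LF/HF are log-transformed before the between-group or group-by-time ANOVA, whatever the Kolmogorov-Smirnov result. Apply the same to plasma cortisol and BDNF if they are compared between groups.
2. Report effects as ratios of geometric means with 95% confidence intervals.
3. Correct the assignment of Mann-Whitney U: keep it for independent-group comparisons and name a paired test for within-group change.

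The cost is two or three sentences, settled before the data are seen, with no extra participants or measurements. The drawback is that results are read as percent differences rather than in raw units.
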